### Ethics

The Central Norway Regional Ethics Health Committee approved the study protocol (REK: 2011/1424 FEST-IT). The study is a replication of a study in adults in which patients in the two treatment groups responded, on average, equally well. The treatment will be manualized. The therapists will be experienced and specially trained, and the therapies will be supervised. Both of the two treatment modalities offered are frequently used, well-established psychotherapy methods. To study adolescent psychotherapy patients with self-rating instruments is a sensitive topic and requires a focus on the integrity of the individuals. No identifiable measures or parts of patient history will be kept outside the patient’s file. Only anonymous data will be kept in the database.

### Eligibility criteria

#### Inclusion criteria

Adolescents with a current *Diagnostic and Statistical Manual of Mental Disorders, Fourth Edition* (DSM-IV; American Psychiatric Association, 2000) unipolar MDD diagnosis will be included. Comorbidity is expected to be frequent. Written consent will be obtained from all patients.

#### Exclusion criteria

Patients with generalized learning difficulties, a pervasive developmental disorder, psychosis or substance abuse will be excluded
[4,26]. To ensure that the sample is diverse and representative of the kind of patients referred to child and adolescent psychiatric outpatient departments and psychiatrists and psychologists in private practice in Norway, no other patients will be excluded.

### Patients

The patients will be recruited from among adolescents with symptoms of depression who are referred to private practice and child and adolescent outpatient departments in the South-Eastern Health Region, primarily in the Oslo area and in Vestfold County. The child and adolescent population in Vestfold County is 52,000, and that in the participating area of Oslo is 13,300. Oslo is an urban area. Vestfold County has rural and urban areas.

One hundred participants will be recruited (Figure
1). The patients will be ages 16 through 18 years. At the first encounter, a referral form will be filled in
[55]. The therapists will explore the patient’s current symptoms and situation, background, and developmental history. As screening tools, the patient will fill in the BDI, a self-report form
[56] and the therapist will fill in the MADRS
[57].

**Figure 1 F1:**
[figure not shown]
CONCORT flow diagram in a randomized controlled trial of dynamic psychotherapy with or without transference interventions (TIs).

### Randomization procedures and methods used to minimize bias

#### Recruitment and baseline procedures

According to the ethical approval, the therapist and not one of the researchers will invite the patient to sign a consent form. If the patient scores above 10 on the BDI and/or above 15 on the MADRS, the therapists will inform the patient about the study and the patients will be asked to give written consent to participate. However, the patient will be advised to discuss this with someone they trust before agreeing to participate. The participants will then be contacted by an interviewer/evaluator, who will schedule an initial meeting. Thus, after the patients agree to participate, but before randomization, they will be diagnostically interviewed by an independent study interviewer using the M.I.N.I. 6.0.0 (Sheehan and Lecrubier, 2010), which is an interview tool used to diagnose psychiatric symptoms according to DSM-IV, and the Structured Interview for DSM-IV Personality (SIDP-IV)
[58]. Before randomization each patient will also have a 1-hour Psychodynamic Interview (PI) modified after Malan
[59] and Sifneos
[60]. If the patient meets the criteria for major depression on M.I.N.I., the therapist (not the interviewer) will contact one of the researchers in the study and the patient will be randomized to one of two treatment groups.

Thus, after consent has been obtained and the baseline assessment has been carried out, a trial ID will be assigned and the randomization will be drawn by one of the main researchers in the study, who will not be the interviewer/evaluator. Only the researcher and the therapist will know the randomization arm. The same interviewer will assess the patient again at the two follow-up evaluations.

Each therapist will treat at least four patients with psychodynamic psychotherapy: two patients with and two patients without transference interventions. Thus, the randomization will be stratified. The order in which each therapist’s patients are allocated to each therapy mode will be drawn by one of the main researchers, a coordinator who will stay in direct contact with the therapist. To minimize bias that could arise from knowledge of treatment allocation, the following strategies will be employed: (1) The interviewers will be blinded to treatment allocation, (2) evaluators and therapists will not communicate with each other about the patient after inclusion, and (3) all evaluation and assessor interviews will be audiotaped and rerated by independent raters, who will be blinded to the randomization. If blindness is broken and the evaluator knows the randomization for one patient, all subsequent assessments will be carried out by an alternative evaluator
[49]. Adherence to the randomization will be evaluated by blind raters by listening to three to five of the audio taped sessions from each patient and scoring them on the Specific Transference Technique Scales
[27].

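### Two-per-arm balance within each therapist lets the unblinded therapist, who also screens and invites patients, deduce some late allocations: about a third if each treats exactly four, 13% to 39% under other plausible schemes

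*Protocol article*

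**What the plan says.** All of this is in the protocol article.

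- **Quota.** Recruitment and baseline procedures: "Each therapist will treat at least four patients with psychodynamic psychotherapy: two patients with and two patients without transference interventions". The next sentence concludes: "Thus, the randomization will be stratified". The stratum is evidently the therapist. No block size is given, nor the number of therapists, nor the rule for patients beyond the fourth.
- **Who draws the order.** The order within therapist is "drawn by one of the main researchers, a coordinator who will stay in direct contact with the therapist".
- **Who knows the arm.** "Only the researcher and the therapist will know the randomization arm".
- **Who screens.** In Patients, the patient completes the BDI and "the therapist will fill in the MADRS". The therapist also takes the history.
- **Who invites.** "the therapist and not one of the researchers will invite the patient to sign a consent form".
- **Who triggers randomization.** After the independent diagnostic interview, "the therapist (not the interviewer) will contact one of the researchers in the study and the patient will be randomized".

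The listed measures against bias are blinded interviewers, no communication between evaluators and therapists about the patient, and blinded rerating of the recordings.

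**The concern.** Concealment requires that whoever decides on entry cannot tell which arm comes next. Here that person delivers every earlier allocation in the stratum and works under a small exact quota. Once one arm's two places are filled, the remaining places are known. The deduction can be made before the next patient is invited, so drawing the arm after consent and baseline does not prevent it.

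A therapist who thinks one technique suits a particular kind of patient could invite, defer or pass over a candidate according to the arm due next. The arms would then differ in prognosis at entry. Blinded rating and intention-to-treat analysis protect measurement and the retention of randomized patients. They do not correct who entered which arm. The history the therapist takes also bears on relational functioning, and quality of object relations is a prespecified moderator, so selection on it could affect the moderator results as well as the main comparison.

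**Working it through.** **The plan's own figure.** The article gives no figure for predictability. Its power statement (Sample size and power: 100 patients, effect 0.55 SD, significance level 0.05, power 0.80) supplies the standard error used below. With 50 per arm, SE = √(2/50) = 0.20 SD. Two-sided normal approximation (sidedness assumed): 0.55/0.20 − 1.96 = 0.79, and Φ(0.79) = 0.785, within two points of 0.80.

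**Step 1: one 2:2 block, six equally likely orders.** An allocation is certain when one arm's quota is used up.

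| Position | Probability certain | Probability best guess is right |
|---|---|---|
| 1 | 0 | 1/2 |
| 2 | 0 | 2/3 |
| 3 | 1/3 | 1/3 × 1 + 2/3 × 1/2 = 2/3 |
| 4 | 1 | 1 |

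Mean certain = (0 + 0 + 1/3 + 1)/4 = 1/3. Mean correct = (1/2 + 2/3 + 2/3 + 1)/4 = 17/24 = 0.708, against 0.5 by chance. With exactly four patients per therapist, 100 patients means 25 therapists and about 33 allocations certain in advance.

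**Step 2: other schemes compatible with a minimum of four.** For a single block with k per arm the certain share is 1/(k+1).

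| Scheme per therapist | Certain in advance |
|---|---|
| Exactly four, or complete repeated blocks of four | 33.3% |
| One block of 3:3, 4:4 or 5:5 | 25%, 20%, 16.7% |
| First four balanced, then simple randomization; 5, 6, 8 or 10 patients: (4/3)/m | 26.7%, 22.2%, 16.7%, 13.3% |
| Block of four, then block of two: (4/3 + 1)/6 | 38.9% |

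**Step 3: possible bias, on the four-patient premise.** Assume that patients invited for one expected arm differ in prognosis from those invited for the other by s = 0.3 to 0.5 SD, and that all therapists steer the same way. The article supplies no value for s.

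- Steering only when certain: bias = s × 1/3 = 0.10 to 0.17 SD.
- Steering on every best guess: bias = s × (2 × 17/24 − 1) = s × 5/12 = 0.125 to 0.208 SD.

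The false-positive rate of an unadjusted posttest comparison with bias b is Φ(−1.96 + b/0.20) + Φ(−1.96 − b/0.20):

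| Bias b (SD) | False-positive rate |
|---|---|
| 0.10 | 7.9% |
| 0.167 | 13.3% |
| 0.125 | 9.6% |
| 0.208 | 18.1% |

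**Step 4: the remedy, four patients per therapist.** A big-stick rule tosses a fair coin unless the imbalance has reached 2, when the lagging arm is forced. Certain by position: 0, 0, 1/2, 0, mean 12.5%. Correct guesses: (0.5 + 0.5 + 0.75 + 0.5)/4 = 56%. The imbalance after four is 0 or 2 with probability 1/2 each, so half of therapists end 3:1.

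- Therapist effects ignored, 25 therapists: expected squared total imbalance = 25 × (1/2 × 4) = 50. Loss = 50/100² = 0.5%.
- Therapist as a fixed effect: information per therapist is 3 × 1/4 = 0.75 against 2 × 2/4 = 1, a 25% loss in half of therapists, or 12.5% on average. SE = 0.20/√0.875 = 0.214, and power = Φ(0.55/0.214 − 1.96) ≈ 0.73.

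**The case against.** **The scheme is not fully stated.** A reader might infer fixed blocks of four and conclude that a third of all the trial's allocations are foreseeable. The article does not support that. It sets four as a minimum, names no block size, and a condensed article may leave sequence generation to the full protocol. This limits the figure but not the mechanism: if the two-per-arm rule holds for a therapist's first four patients and the therapist knows it, the last of those places is always deducible.

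**Disclosure by the coordinator.** A reader might also take "a coordinator who will stay in direct contact with the therapist" to mean that the upcoming order is passed on. The phrase describes coordination and does not say so. The point rests on deduction from the quota, not on disclosure.

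**Entry is not wholly discretionary.** Invitation follows score thresholds, the BDI is completed by the patient, Exclusion criteria allows no exclusions beyond those listed, and an independent interviewer must confirm major depression before randomization. Inviting by expected arm would breach the protocol. This narrows the room for steering. But the interviewer sees only patients already invited and cannot detect an eligible patient who was deferred or never asked.

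**The analysis gives partial protection.** The planned mixed model uses all data including baseline, contains quality of object relations and has no treatment main effect at baseline. Selection on baseline severity or on that covariate would be partly adjusted. Selection on unmeasured prognosis would not.

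**The bias figures take a common direction.** This stands. Opposite preferences among therapists would offset one another.

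**Balance within therapist has a purpose.** It separates technique from therapist, which matters in a dismantling design. That is an argument for restricting imbalance; it does not require an exact, deducible quota.

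**Conclusion.** The concern holds as a weakness of allocation concealment. The therapist who screens, invites and triggers randomization can know some late allocations before inviting a patient, and none of the listed safeguards addresses this.

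The size is conditional. One third certain and 71% correct guesses apply to exactly four patients per therapist or complete repeated blocks of four, with therapists who know the rule. Across the other schemes tried, about 13% to 39% are certain. The bias of 0.10 to 0.21 SD and false-positive rate of about 8% to 18% further assume a common direction of steering, an assumed 0.3 to 0.5 SD difference in prognosis, and no baseline adjustment. They show what could happen. A reader should not infer that steering is occurring or that the result will be biased by that amount; the article contains no evidence of either. Even so, 0.21 SD would be more than a third of the planned 0.55 SD effect (0.208/0.55 = 0.38), and lost concealment cannot be fully repaired in the analysis. The plan should be changed while patients remain to be randomized.

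**What to change.** Trial status describes the study as ongoing, so the change can apply to all remaining patients:

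- Replace the exact two-per-arm quota with a restricted random sequence within therapist that cannot be fully deduced, for example a big-stick or biased-coin rule with maximum imbalance 2.
- Have it generated and released one patient at a time, after baseline, by an existing team member who has no contact with the therapists.
- Include therapist in the analysis model.

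With four patients per therapist under big-stick, certain allocations fall from 33% to 12.5% and correct guesses from 71% to 56%. Some predictability remains: the third allocation is certain in 1/2 of cases instead of 1/3, while the fourth is no longer known.

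The administrative cost is a new list and a short protocol change. The statistical cost should be stated openly. The two-per-arm rule is relaxed, and about half of therapists with four patients would end 3:1. The information loss is about 0.5% if therapist effects are ignored and up to 12.5% with therapist as a fixed effect. In the latter case power at 0.55 SD falls from about 0.785 to about 0.73, the worst case.

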### Interventions: short-term psychodynamic/psychoanalytic psychotherapy (STPP) with transference interventions in comparison with STPP without transference interventions

#### Therapists

The patients will be treated by specially trained therapists. The therapists will be specialists in child and adolescent psychiatry, psychiatry or clinical psychology and will have at least 2 years of formal education (that is, practical and theoretical) in psychodynamic psychotherapy. They will be further trained in a 1-year program to provide dynamic psychotherapy with a moderate frequency of transference interventions (one to three per session) and dynamic psychotherapy without transference work. Peer supervision in groups will be offered to the therapists. This will help to maintain the quality of the therapies.

#### Treatment condition

Short-term psychodynamic/psychoanalytic psychotherapy (STPP) is a well-known treatment model
[61,62]. The STPP manual from the IMPACT study
[63] will be used as the manual for the treatment. The manual combines aspects of STPP that focus principally on techniques aimed at helping young people overcome developmental problems, as well as emphasizing the role of the interpretation of unconscious conflicts, attachment theory and the concepts of internal working models. With the agreement of the adolescent, parallel work with parents is included. Antidepressant medication may be added in severe cases according to the national guidelines in Norway
[12]. FEST-IT will be an experimental study of the effect of dynamic psychotherapy with transference interventions on adolescents with depression
[61,64]. The patients will be randomized to two treatment groups. The treatment in both groups will use general psychodynamic techniques
[63]. The patients will be given 45-minute sessions. The treatment period will be 28 weeks. Therapies lasting less than 12 hours will be defined as dropouts. In the transference group, specific techniques will be prescribed, including the therapist (1) addresses transaction in the patient–therapist relationship, (2) encourages exploration of thoughts and feelings about the therapy and the therapist, and (3) interprets direct manifestations of transference and links repetitive interpersonal patterns to transactions between the patient and the therapist. In the comparison group, these techniques will be proscribed. In this group, the therapist will consistently use material about interpersonal relationships outside therapy as the basis for similar interventions (extratransference interventions). That means that in the transference group, analysis of the transference will be used with moderate intensity, whereas in the comparison group the therapists will avoid focusing on the patient–therapist relationship. Both treatments are mainly exploratory in nature. Patients in both treatment groups will be encouraged to explore sensitive topics. If the patient agrees, the parents and/or caregivers will be offered consultation by another therapist.

### Assessments and outcomes

#### Pretreatment: Interviews

Before randomization, each patient will be diagnosed according to DSM-IV criteria (M.I.N.I.6.0.0, SIDP–IV). See FEST-IT assessment battery (Table
1)Based on the information derived from an interview about present symptoms and situation, background and development history, as well as from information obtained from the Psychodynamic Interview (PI) (Sifneos
[60] and Malan
[59]), the patient’s Quality of Object Relations (QOR–2; relations to others and relation to family), the pretreatment scores on Global Assessment of Function Scale (GAF) over the past 2 weeks, and PFS
[50] will be scored by two blinded raters. The Psychodynamic Functioning Scales (PFS) have the same format as GAF and measure psychological functioning. The six scales are as follows: Quality of Family Relationships, Quality of Friendships, Quality of Romantic/Sexual Relationships, Tolerance for Affects, Insight, and Problem Solving Capacity. Aspects of content validity, internal domain construct validity, interrater reliability, discriminant validity from symptom measures, and sensitivity for change in brief dynamic therapy have been established. In FEST–IT five of the six subscales will be used (quality of family relations, quality of friendships, tolerance for affects, insight, and problem-solving and adaptive capacity)
[51,65,66]. The Differentiation-Relatedness Scale (DRS)
[67] will also be scored by two blinded raters on the basis of the audiotaped interview.

**Table 1 T1:** **Assessments administered at research baseline and each follow-up point throughout the trial**^**a**^

**Assessment points**	**Interviews**	**Measures**	**Self-report Questionnaires**	**Therapist questionnaires**
Baseline (0 weeks)	M.I.N.I., SIDP–IV, PI	QOR–2, PFS, GAF, DRS	BDI, PBI, Exp IIP–C, SCL–90, ARS,	MADRS
After session 3			WAI	WAI, FWC–24
After session 12			WAI, BDI, IIP–C, SCL–90, ARS	WAI, FWC–24, MADRS
After session 20			WAI, BDI	WAI, FWC–24, MADRS
Posttreatment	M.I.N.I., SIDP–IV, PI	PFS, GAF, DRS	WAI, BDI, IIP–C, SCL–90, ARS	WAI, FWC–24, MADRS
1-year follow-up	M.I.N.I., SIDP–IV, PI, MADRS	PFS, GAF, DRS	BDI, IIP–C, SCL–90, ARS	

^a^ARS, adolescent relationship scale; BDI, Beck Depression Inventory; DRS, Differentiation–Relatedness Scale; Exp, global expectancy; FWC–24, Feeling Word Checklist–24; GAF, Global Assessment of Functioning; IIP–C; Inventory of Interpersonal Problems–Circumplex Version; MADRS, Montgomery Åsberg Rating Scale; M.I.N.I., Mini-International Neuropsychiatric Interview; PBI, Parental Bonding Instrument; PI, psychodynamic interview; PFS, Psychodynamic Functioning Scale; QOR–2, Quality of Object Relation Score; SCL–90, Symptom Checklist–90; SIDP–IV, Structured Interview for DSM–IV Personality; WAI, Working Alliance Inventory.

#### Self-report

At pretreatment, the patient will complete the IIP-C
[52], SCL-90
[53], and Parental Bonding Instrument Mother and Father (PBI)
[68]. The patients will score the Adolescent Relationship Scale (ARS) which are visual analogue scales (VASs) used to evaluate the importance of friends, parents, siblings and quality of life
[69], and the Global Expectancy (Exp), a visual analogue scale for patients
[49] which indicates the confidence that the treatment will be helpful, will also be filled in.

#### During treatment

Working Alliance Inventory, the short form with 12 items (WAI)
[70-72], will be filled in by the patient after sessions 3, 12, and 20. After session 12, the patients will also fill in the IIP–C, SCL–90-R, ARS and BDI. The WAI and Feeling Word Checklist–24 (FWC–24)
[73] will be filled in by the therapist after sessions 3, 12 and 20. MADRS will be filled in after sessions 12 and 20.

#### Posttreatment

After session 28, the therapist will fill in the WAI, MADRS and Feeling Word Checklist–24. The patients will fill in the IIP–C, SCL–90-R, ARS, BDI and WAI. A blinded evaluator will interview the patient using the M.I.N.I. and SIDP–IV. PFS and GAF will be scored by two blinded raters on the basis of an audiotaped interview. The DRS will be scored.

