### Aims

The primary hypothesis is that the transference group will have a more favorable course than the comparison group over time (that is, a significant improvement on the Psychodynamic Functioning Scales (PFS) and Inventory of Interpersonal Problems–Circumplex Version (IIP-C) and the measured depression by Mini International Neuropsychiatric Interview (M.I.N.I.), Beck Depression Inventory (BDI) and Montgomery Åsberg Rating Scale (MADRS) during the whole study period). The second hypothesis is that patients with a history of low QOR scale score and/or lacking personality disorders benefit more from therapy with transference work than from therapy without it. The third hypothesis is that female adolescents have better treatment effect of transference work than male adolescents do.

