### Planned investigations

FEST–IT will be a randomized trial that compares short-term psychodynamic psychotherapy with and without transference interpretation to reduce relapse in adolescents with DSM-IV-defined MDD. The patients will be randomly allocated to STPP with or without transference interventions. This is a dismantling design in which a single component is added and/or varied to an existing treatment approach. The therapy is manualized. Outcomes will be assessed at planned follow-up points by outcome evaluators unaware of the treatment allocation. The therapists will be psychodynamically trained therapists who will undergo a 1-year training program succeeded by peer supervision in groups. This will help maintain the quality of the therapies. The therapies will be audiotaped to evaluate treatment adherence.

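### The posttreatment MADRS, part of the primary hypothesis, is rated by a therapist who knows the arm, against the protocol's blinding statement; Table 1 and the text disagree on MADRS at 1 year

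*Protocol article*

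**What the plan says.** - **Role of MADRS.** The primary hypothesis in Aims covers PFS, IIP-C and "the measured depression by Mini International Neuropsychiatric Interview (M.I.N.I.), Beck Depression Inventory (BDI) and Montgomery Åsberg Rating Scale (MADRS"), over the whole study period. The Discussion gives a different list: PFS-5 and IIP-C are primary, GAF and GSI secondary, and MADRS is in neither group.
- **Who knows the allocation.** Recruitment and baseline procedures: "Only the researcher and the therapist will know the randomization arm".
- **Who rates MADRS.** At screening, before randomization, "and the therapist will fill in the MADRS" (Patients). For the treatment period the text says only that "MADRS will be filled in after sessions 12 and 20" and names no rater; Table 1 puts both ratings under therapist questionnaires. After treatment, "After session 28, the therapist will fill in the WAI, MADRS and Feeling Word Checklist", and Table 1 agrees.
- **MADRS at 1 year.** The Interviews cell of Table 1 reads "M.I.N.I., SIDP–IV, PI, MADRS" and the therapist column is empty. The 1-year follow-up text has a blinded evaluator conduct the M.I.N.I. and SIDP-IV and does not mention MADRS.
- **Blinding.** Planned investigations: "Outcomes will be assessed at planned follow-up points by outcome evaluators unaware of the treatment allocation". The section on minimizing bias has evaluation and assessor interviews taped and rerated by blinded raters, and replaces an evaluator who learns a patient's allocation.
- **Analysis.** The Statistical analysis plan section fits a linear mixed model to all data over the whole study period, with the treatment effect carried by time × treatment.

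**The concern.** MADRS is a clinician-judgement scale, and after randomization it is scored by the person who delivers the treatment and knows which version it is. At posttreatment this is incompatible with the statement that follow-up outcomes are assessed without knowledge of allocation. A reader of the protocol would take the MADRS comparison to be blinded when it is not. If therapists favour one technique, their scores could show a difference between arms that patients did not experience, and no later analysis can restore the blinding.

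The 1-year entry adds a second difficulty. On Table 1 the rater appears to change between posttreatment and 1 year, the interval in which relapse would show. On the text it is unclear whether MADRS is rated at 1 year at all.

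**Working it through.** **1. MADRS ratings by time point**

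| Time point | Rater | Knows arm? | Basis |
|---|---|---|---|
| Baseline | Therapist | No, precedes randomization | Patients; Table 1 |
| Session 12 | Therapist | Yes | Table 1 only |
| Session 20 | Therapist | Yes | Table 1 only |
| Posttreatment | Therapist | Yes | Posttreatment text; Table 1 |
| 1 year | Apparently the blinded evaluator | Apparently no | Inferred from Table 1; text omits MADRS |

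Three of the five ratings are made by someone who knows the arm.

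**2. Where the contradiction lies.** The blinding sentence concerns planned follow-up points. Recruitment and baseline procedures speaks of two follow-up evaluations by the interviewer, which in Table 1 are posttreatment and 1 year. Sessions 12 and 20 are therefore outside that sentence, and the direct conflict is the posttreatment MADRS. The rerating safeguard covers interviews, not therapist questionnaires, so it does not remove the conflict.

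**3. How a bias would act.** Write the expected rating at time t as

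μ(t) + δ(t)·arm + r(t) + b(t)·arm,

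where δ is the true arm difference, r the general level of whoever rates at t, and b that rater's arm-specific bias. The difference between arms at t is δ(t) + b(t), because r(t) cancels.
- b is 0 at baseline (arm not yet assigned) and 0 under a blinded rating at 1 year. It can differ from 0 at sessions 12, 20 and posttreatment, and there it goes into time × treatment.
- A change in r from posttreatment to 1 year shifts both arms equally. It alters the time term, not time × treatment.
- If b is not 0 at posttreatment and is 0 at 1 year, the arm difference changes by −b over that interval in addition to any true change.

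**4. The plan's own figure.** Inputs from Sample size and power: 100 patients (taken as 50 per arm), effect size 0.55, α = 0.05 (taken as two-sided). The standard error of the difference in SD units is √(2/50) = 0.2. Power ≈ Φ(0.55/0.2 − 1.96) = Φ(0.79) = 0.785, against the stated 0.80, so it reproduces approximately. The present point does not depend on it.

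**5. Illustration on the same basis.** The bias b is assumed, because the protocol gives no value. With no true effect, the rejection rate is Φ(b/0.2 − 1.96) + Φ(−b/0.2 − 1.96).

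| b (SD) | b/0.2 | Rejection rate, normal | Noncentral t |
|---|---|---|---|
| 0 | 0 | 0.050 | 0.050 |
| 0.1 | 0.5 | 0.079 | 0.079 |
| 0.2 | 1.0 | 0.170 | 0.168 |
| 0.3 | 1.5 | 0.323 | 0.318 |

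This is a comparison at one time point, not the planned longitudinal model.

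**The case against.** **MADRS may not be a primary outcome.** The Discussion, where primary and secondary status is assigned, omits it. That stands and limits the consequence, but Aims still puts MADRS in the primary hypothesis and the two sections are not reconciled.

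**The blinding sentence may mean only evaluator-rated measures.** It cannot literally cover BDI and IIP-C, which are self-report, and Table 1 openly lists MADRS as a therapist questionnaire. That is a fair reading, but the sentence carries no such limit and MADRS is clinician-rated.

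**The design balances therapists.** The same therapists are trained in both conditions, and each treats at least two patients per arm under stratified randomization. General leniency, or optimism about one's own patients, therefore largely cancels. What remains is a preference for one technique, because the therapist knows each patient's arm. The protocol gives no evidence of its size or direction.

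**Stronger readings that the protocol does not support.** A reader might infer that outcome blinding fails throughout. It does not: PFS and GAF are scored by two blinded raters, the M.I.N.I. is done by a blinded evaluator, and IIP-C and BDI come from patients described as unaware of their group. A reader might also infer that the change of rater by itself biases the treatment effect. A shift common to both arms does not. Nor does any text state that the blinded evaluator rates MADRS at 1 year; that is an inference from a table column.

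**Conclusion.** The point holds for MADRS only. The posttreatment rating by a therapist who knows the arm contradicts the protocol's statement on blinded assessment, and no stated safeguard covers it. The ratings at sessions 12 and 20 are unblinded too, according to Table 1, but do not contradict that statement. Table 1 and the 1-year text disagree and must be reconciled.

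The size of any bias is unknown. The rise from 5% to about 8%, 17% or 32% rests on assumed biases of 0.1, 0.2 or 0.3 SD, 50 per arm, no true effect and a single time point. It shows how sensitive a MADRS comparison would be and is not an estimate of this trial's type I error. The PFS-5 and IIP-C comparisons are unaffected.

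**What to change.** **Preferred, for patients still to be assessed.** Keep the therapist MADRS at screening, where it helps decide who is invited. Have the blinded evaluator also complete MADRS at the existing baseline, posttreatment and 1-year interviews. Use only these blinded ratings to compare arms, and report therapist ratings descriptively. Change Table 1, Posttreatment and 1-year follow-up to match.

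**For patients already assessed, or if this is not feasible.** State that the therapist MADRS is unblinded and qualify the sentence in Planned investigations. Remove MADRS from the primary hypothesis, in line with the Discussion, which leaves the self-reported BDI and the blinded M.I.N.I. for depression. Limit the MADRS arm comparison to the blinded 1-year rating, and align Table 1 with the 1-year text on whether and by whom it is done.

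**Cost.** The preferred route adds a few minutes per interview, with no new visit. The alternative costs only wording and the choice of analysis. Because the trial is ongoing, patients already past posttreatment will have no blinded MADRS at that point, and a series that combined their therapist ratings with later evaluator ratings would again mix raters.
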